### 2.4. Intervention

There will be two main components to the intervention. A self-directed learning package known as the ‘Aroha Passport’ (Aroha is an indigenous Māori concept that not only incorporates empathy, but also love and compassion and is a deeply emotional way of thinking and being) and researcher-facilitated ward activities.

*Aroha Passport.* The primary aspect of the intervention is facilitating a self-directed learning experience through easily accessible resources. The ‘Aroha Passport’ will be a pocket-sized booklet that consists of eight-weeks of short activities, including reading or writing activities, engaging with work colleagues and short videos relating to a weekly topic (see Appendix A). Each week, the healthcare team will be asked to reflect on a Māori whakataukī (indigenous New Zealand proverb) as well as Western and Eastern ideas to build an understanding of both empathy and how participants relate and respond as people. Participants will be expected to work through the activities and complete the passport in their own time. The time to complete an activity will vary between 2 min and 40 min. Reminders of the activities will be provided via email messages.

*Ward Activities.* The ward will be ‘branded’ with a weekly focus corresponding to the weekly topic of the Aroha Passport. A dedicated staff quiet space for healthcare workers, known as the *Empathy Station*, will be located on the ward. In this space of respite, HW participants will be given a white board activity to reflect on the weekly Māori whakataukī (proverb). These activities include prompts as “What are you going to do this week to take care of yourself?” or “Write a kind word to your patients.” The research team will have an active presence at the empathy station to answer questions and accompany visiting healthcare workers. To demonstrate and role model empathy, a twice daily *hydration station* will be part of the education package. Research team members will walk around with a refreshment trolley, offering different herbal/fruit teas, cold water and occasionally fruits, biscuits, and home baking to working healthcare staff. All other times, the trolley will be located in the empathy station where night staff can access the refreshments. During weekdays, team members will also facilitate a daily 5-min *mindfulness* practice in a designated room with dimmed lighting. These sessions will be either guided by a team member or played from different mindfulness mobile apps to provide a wide variety of experiences to the healthcare staff.

## 3. Measures and Outcomes

### 3.1. Feasibility Outcomes

The feasibility of a prospective CRT on enhancing empathy in the clinical setting will be estimated based on the acceptability of the intervention (1) and the estimated organisational resources needed to continue the programme (2). First, the acceptability of the intervention will be assessed both quantitatively and qualitatively: (a) analysing recruitment, completion, and drop-out rates; (b) monitoring active and passive participation in the intervention; (c) optional weekly written feedback from healthcare worker participants; (d) surveying healthcare worker participants about their prior expectations of the intervention and whether their expectations were met after the intervention; (e) and focus group interviews with approximately 5–10 healthcare worker participants. The main objective of the focus groups is to review and evaluate the EmpEd from the participants’ perspective: evaluation of quality and mode of delivery, usefulness, staff engagement, and specific components of the intervention. Second, to determine the resources needed by the organisation to run an EmpEd, the following need to be considered and estimated: (a) scientific personnel for EmpEd training and supervision; (b) clinical networks and cooperation; and (c) equipment and material costs. Importantly, the EmpEd programme review is not only to measure the feasibility, engagement, and applicability of the programme, but also to assess the viability of continuing aspects of the immersion programme, for example, regular mindfulness sessions or the hydration station.

### 3.2. Efficacy Outcomes

To determine the efficacy of a prospective CRT on enhancing empathy in the clinical setting, we will use quantitative scientific assessment of both HWs and HCs over time. The primary efficacy outcomes will focus on HWs’ empathy levels and their ‘professional wellbeing’ in terms of organisational satisfaction, burnout and work-related positive–negative emotions, which are assessed by three pre-existing scales. Our use of these standardised tools will aid comparability with other studies in subsequent publications.

The *Interpersonal and Social Empathy Index (ISEI*) is a multidimensional measure of empathy, assessing macro perspective taking, cognitive empathy, self–other awareness, and affective response [28]. This 15-item index requires participants to rate the frequency of their experiences about different aspects of empathy on a 5-point scale from 1 (*Never)* to 6 (*Always*). For example, “When I am with someone who gets sad news, I feel sad for a moment too” and “I am good at understanding other people’s emotions”. Items will be averaged to create four distinct scales in which higher scores will indicate higher levels of macro perspective taking, cognitive empathy, self–other awareness, and affective response.

The *Employee Organisation Satisfaction Scale* (*EOSS*) will be used as a proxy to measure the quality of the emotional culture of the clinical unit. This 10-item scale requires participants to indicate their agreement with statements about how they feel towards their organisation (1 = *Strongly disagree*, 5 = *Strongly agree*). For example, “I would recommend my unit as a good place to work” and “At work, my opinion seems to count”. Items will be averaged so higher scores will indicate higher levels of organisational satisfaction as an indicator of healthy emotional ward culture.

The *Professional Quality of Life Scale (ProQOL)* [29] consists of two aspects of one’s feelings about their professional life: a positive (compassion satisfaction) and a negative aspect (compassion fatigue). Compassion satisfaction reflects the pleasure and satisfaction a person derives from their ability to do their work well and to be an effective caregiver. Compassion fatigue is divided into two parts. The first part assesses psychological aspects typical of burnout (e.g., exhaustion, frustration, and depression). The second part focuses on work-related, secondary exposure to extremely stressful events, known as secondary trauma. Each subscale is psychometrically unique and hence does not yield a composite score. Each subscale consists of 10 items, and participants are asked to rate the frequency of their experiences from 1 (*Never)* to 5 (*Very often)*. Items will be averaged together to create three distinct scales. Higher scores will indicate greater work-related satisfaction; a greater risk for job related burnout; and a greater exposure to secondary traumatic stress.

Additionally, at three time points, HW participants will provide answers to open-ended questions about aspects of their professional life related to empathy, for instance, describing their ability to empathetically relate to others in the workplace, sharing the most challenging aspect of expressing empathy towards others and if there is anything that they would like to improve about their ability of relating to others. Qualitative analyses of these written responses will be used to complement the quantitative data on understanding the efficacy outcomes of the EmpEd.

The secondary efficacy outcomes focus on HCs’ experiences of the healthcare team’s empathetic care and support over time. The same survey tools will be administered to HCs who will differ across time points:

The *Consultation and Relational Empathy Measure (CARE)* [30] is a 10-item scale that assesses healthcare consumers’ perception of relational empathy in healthcare workers’ communication. The CARE measure has previously shown good validity and reliability in primary and secondary care [30,31], and has successfully been used to detect change in patients’ perception of resident physicians’ empathy [24]. Instructions will be slightly modified to ask participants to rate the quality of *support* they will have received during their hospital stay/visit (1 = *Poor*, 5 = *Excellent*, with an additional “does not apply” category for each item). Example items include “How good the healthcare team was at making you feel at ease” and “… allowed you to tell your story”. Items will be averaged so that higher scores will indicate higher perceived quality of support.

The *Australian Hospital Patient Experience Question Set (AHPEQS*) will assess patients’ experiences of treatment and care [32]. Participants will rate their level of (dis)agreement with eight statements on a 7-point scale (1 = *Strongly disagree*, 7 = *Strongly agree*, with an additional “does not apply” category). For example, “When a need couldn’t be met, staff explained why”. The AHPEQS measure has previously shown good validity and reliability for patients in hospital care across Australian states [32]. We will trial this measure for use in New Zealand. This trial will support the national assessment of patient experiences in New Zealand undertaken by the Health Quality & Safety Commission [33].

*Measuring HCs’ experiences among visiting support persons.* Both the *CARE* and *AHPEQS* survey tools were designed to assess patients’ experience. There is a lack of validated survey tools assessing satisfaction and quality of care among visiting support persons (e.g., family members of hospitalised patients). Assessing visiting support persons’ views is essential not only for understanding the needs of the wider HC group, but it has pivotal importance in cases where hospitalised patients are unable to participate due to cognitive impairment. For this purpose, the patient experience scales were adapted to measure visiting support persons’ experiences. The survey items remained the same but were reorientated to the perspective of the visitor about their *own* experience of HWs’ treatment of *them* as visitors.

Similarly, qualitative data will be collected in a written format from HC participants about their experience of HWs’ treatment of them on a human level, and whether there is anything more that they wish staff would do for patients and their support persons.

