## 2. Method

### 2.1. Design

This quasi-experimental study of healthcare workers and healthcare consumers is a feasibility and pilot study to form the basis for a future, prospective cluster randomised trial (CRT). The single centre study will be conducted at one tertiary hospital in New Zealand. To minimise harm to participants, the key characteristics that will guide the ward selection are stable workforce, predictable patient population, and stable leadership. Based on local conditions, the Chief Nursing Officer will identify and select two wards (intervention and control ward) that meet these criteria. Although everyone on the wards will be invited to participate in the study, it is reasonable to expect that not everyone would want to be enrolled in the research. Thus, the wards are the study setting, and the groups are the enrolled participants on the wards.

Participants will be pre-allocated into four groups. Based on the participants’ location in the hospital, they will be either part of the intervention or the control group. Based on the participants’ position in the healthcare system, they will be either part of the HW group or the HC group. Participants in the HW groups will be constant during the study, while participants in the HC groups will differ across time points. HWs in the intervention ward/group will receive an 8-week immersive empathy education programme and the control ward/group will operate as usual during the research study. HCs will receive care, support and will interact with healthcare workers as usual in both wards/groups. HCs in the intervention ward/group will not be directly affected by the intervention; however, they will experience limited exposure to the education programme (e.g., seeing educational materials on the ward walls).

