The study duration is expected to be approximately 30 weeks (see Figure 1 for the outline timetable for participants). The study will begin with a 3-week recruitment and consenting period prior to delivering the intervention. Baseline assessment of all participants will be continuous in this 3-week period (Weeks 1–3). This is followed by the 8-week intervention. The research team will deliver the immersion programme in the intervention ward, while the control ward will continue to operate as usual with no interaction/engagement during this time with the research team (Weeks 4–12). After delivering the intervention, all participants will complete the second assessment (Week 13–15). HWs in the intervention ward will be invited to participate in focus group interviews about their experiences of the EmpEd (initiation, Week 13; interviews, Weeks 16–17). Three months later, a final follow-up assessment of all participants will complete the quasi-experiment (Weeks 27–30). The design is adaptive in that the study duration and the intervention can be changed if participation and feedback from study participants indicate necessary adjustments for successful study continuation.

An advisory group will be established, and will be made up of health care professionals, healthcare consumer representatives, cultural advisors, and international experts in empathy education. The purpose of the advisory group is to ensure that relevant perspectives and voices are heard and considered in the design of the intervention and the assessment of the EmpEd (e.g., considering different value orientations in a multicultural environment, the work schedule of HW participants, and access to resources). Three advisory meetings will be held over the course of the programme, and a 100 NZD gift voucher per meeting will be offered to each advisor for their contribution.

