### 2.2. Participants

A convenience sample of HW and HC participants will be recruited to complete the study. Participants must provide written, informed consent before any study procedures occur. Eligibility criteria will differ across groups.

HW participants will consist of both registered and non-registered staff, including pharmacists, physiotherapists, occupational therapists, social workers, nurses, doctors, health care assistants, ward clerks, and domestic services staff. With an estimated drop-out rate of 25%, we will recruit up to 138 healthcare worker participants to ensure completion of 110 (55 per ward). Inclusion criteria for healthcare worker participants include (a) being employed in the clinical sites and (b) giving informed consent. Exclusion criteria include (a) working across both the intervention and control wards; (b) agency staff working across multiple wards; or (c) being a medical student, a nursing student, or an allied health student.

HC participants will consist of hospitalised patients and their visiting support persons. With an expected non-completion rate of 10%, we will recruit up to 165 participants to ensure completion of 150 (75 per ward with 25 per timepoint) to complete the study. Inclusion criteria for healthcare consumer participants include (a) ability to understand, read and write English; (b) capacity to give informed consent; (c) (for patients only) being ready for discharge—this is to allow patients to reflect on their experiences and interactions in a non-acute phase of their illness; and (d) (for support persons only) have been actively supporting the patient during their admission (i.e., visited patient at least once per week). Exclusion criteria include (a) being unable to give informed consent; (b) being under the age of 18 years; (c) (for patients only) not predicted to be discharged from the ward between the data collection periods; and (d) (for support persons only) have not been involved in regular support of the patient (i.e., visited less than once a week).

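### The CARE instruction asks about the whole hospital stay, while the programme and the grouping are by ward, so ratings can include care from units that were never trained

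*Protocol article*

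**What the plan says.** Section 3.2 of the protocol article describes CARE as a ten-item consumer rating of relational empathy. Its instruction is to be slightly altered so that respondents rate the support "they will have received during their hospital stay/visit". One example item reads "How good the healthcare team was at making you feel at ease". No ward is named in the wording shown.

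Exposure is defined at ward level. Section 2.1 states that "HWs in the intervention ward/group will receive an 8-week immersive empathy education programme", with a second ward as control. The same section allocates participants as follows: "Based on the participants’ location in the hospital, they will be either part of the intervention or the control group".

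In section 2.2, patients qualify by "for patients only) being ready for discharge", and the related exclusion concerns expected discharge from the ward. Neither criterion sets a minimum time on the ward, limits the admission date or deals with transfers from other units.

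On timing, section 2.1 places the programme in Weeks 4–12, the second assessment (T2) in Weeks 13–15 and the final one (T3) in Weeks 27–30. Section 3.3 labels the consumer part exploratory and open to change.

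**The concern.** The period a respondent is asked to rate should match the exposure being compared. Here the exposure is one ward's staff, but the period is the hospital stay. A patient in a tertiary hospital may spend time in another unit before reaching the study ward. Such a patient is eligible once ready for discharge, however short the time on the ward, and is asked about support that came partly from staff with no part in the programme.

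The article guards against this kind of mixing among staff: section 2.2 excludes workers shared between the two wards and agency staff who cover several. It has no matching guard for consumers.

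The likely consequence is a consumer difference pulled towards zero. This matters beyond the pilot because the study is meant to inform a cluster randomised trial, and the instruction could be carried into it. A rating collected with the wrong frame cannot be re-framed afterwards.

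**Working it through.** **The plan's own consumer figure.** Section 3.3 gives a confidence limit of ±0.139 for a proportion of 0.5 with 50 per ward per time point. Check: 1.96 × √(0.5 × 0.5 / 50) = 0.1386, so it reproduces, and 50 × 3 time points × 2 wards = 300 as stated. At the planned 25 per ward per time point (section 2.2) the half-width is 1.96 × √(0.25 / 25) = 0.196. The reference period of CARE changes neither figure.

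**Rating period against exposure.**

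| Element | Defined by | Section |
|---|---|---|
| Programme delivery | Ward | 2.1 |
| Consumer group | Ward (location) | 2.1 |
| Patient eligibility | Readiness for discharge; no minimum ward time | 2.2 |
| Period rated on CARE | Hospital stay or visit | 3.2 |

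The last row is the only one not tied to the ward or to leaving it.

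**Dilution.** Assume a rating reflects care in proportion to where it was received, that a share f came from other units, that care there is unaffected by the programme, and that f is the same for both wards. A true ward-level difference δ then appears as (1 − f) × δ. The sample needed to see it with equal certainty grows by 1 / (1 − f)².

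| Assumed f | Effect remaining | 1 / (1 − f)² |
|---|---|---|
| 0.1 | 90% | 1.23 |
| 0.2 | 80% | 1.56 |
| 0.3 | 70% | 2.04 |
| 0.5 | 50% | 4.00 |

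The documents do not give f. The last column only shows scale: the consumer part is sized by interval width, so there is no planned effect or power to set it against.

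**Overlap of T2 stays with the programme weeks.** Assume discharges spread evenly over the 21 days of Weeks 13–15, a programme ending at the close of Week 12, and a fixed stay of L days (L ≤ 21). The share of patients whose stay reaches back into the programme is L / 21. The mean share of a stay inside it is (L² / 2) / (21 × L) = L / 42.

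| Assumed L | Patients with any overlap | Mean share of stay in programme |
|---|---|---|
| 3 days | 14% | 7% |
| 7 days | 33% | 17% |
| 14 days | 67% | 33% |

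Weeks 4–12 counted inclusively are nine calendar weeks for an eight-week programme. If delivery ended with Week 11, a 7-day stay would not overlap at all. A 14-day stay would overlap for (14 − 7) / 21 = 33% of patients, with a mean share of 7² / (2 × 21 × 14) = 8%. Length of stay is not given, so these figures show only that the overlap could range from negligible to substantial and that an admission date would be needed to describe it.

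**The case against.** The strongest reply is that the article paraphrases the instruction and the questionnaire is not shown. The visible cues may steer answers to the ward: the item asks about the healthcare team, consumers are approached in person on the ward, and patients answer shortly before leaving it. Support persons rate how they themselves were treated as visitors, so for them the frame is already close to the ward. The wards are also chosen partly for a predictable patient mix. All this stands as a reason why the dilution may be small. It does not remove the mismatch, because the period as stated is the hospital stay and nothing in the article narrows it.

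It is also fair that this is one secondary efficacy instrument in an exploratory part of a feasibility study, and that every value of f above is an assumption. That limits the weight of the point.

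A reader might go further and infer that T2 is contaminated by care given during the programme, so that change from T2 to T3 cannot be interpreted. The documents do not support this. Care on the intervention ward in Weeks 4–12 came from staff already receiving the programme, so it is at least partly exposed care. No section defines T2 as rating post-programme care only. Section 2.1 openly expects consumers to have some limited contact with the programme. T3 lies well clear of it unless stays are very long.

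**Conclusion.** The point holds in a limited form. As stated, the CARE rating period is wider than the ward-level exposure, and no eligibility rule closes the gap, so ratings can include care from untrained staff elsewhere. It cannot be said that they do, or how often, because the article gives neither a transfer rate nor a length of stay.

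The expected direction is dilution of the between-ward consumer comparison, leaving about (1 − f) of the effect. This rests on care elsewhere carrying no programme effect and on f being alike in the two wards. A reader might infer that the wards are diluted to different degrees; that is possible, but nothing in the article bears on it.

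The overlap of T2 stays with the programme weeks is something to describe, not a flaw in the design. The primary feasibility outcome, the healthcare worker outcomes and the stated sample-size figures are untouched.

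**What to change.** In section 3.2, word the modified CARE instruction so that it asks about support received during the respondent's stay on this ward (patients) or visits to this ward (support persons). Record the date of admission to the ward on the consumer form, so that time on the ward, and any overlap of T2 stays with the programme weeks, can be described.

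The cost is a few words in an instruction already being changed and one date field. The downside is slightly less comparability with uses of CARE that ask about the whole stay.

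Two further steps may look natural but are not advised:

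- **Rewording AHPEQS in the same way.** The article states no reference period for that tool, and it is being trialled to support national patient-experience measurement, where a changed frame would work against that aim.
- **Restricting T2 to ward stays that began in Week 13 or later.** With the window closing in Week 15, this selects short stayers at T2 but not at the other time points, and so distorts the comparison over time. It would also shrink groups of about 25.
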